### Routine psychological care

The control group receives routine psychological care, graded care based on the psychological assessment of women upon admission [27]. Specific Content: (a) women in good psychological states receive general psychological comfort from nurses, explanations about fetal abnormalities, induced labor, postpartum care, and preparation for future pregnancies; (b) for women with mild to moderate psychological issues, nurses develop a psychological counseling plan involving family members; (c) women with severe psychological disorders require counseling under a psychological expert’s guidance or are advised to seek psychiatric psychotherapy. Researchers will offer MBCI and related guidance to participants at the study’s end, considering ethical concerns.

### Intervention fidelity

A senior psychological counselor supervises the entire intervention process. The mindfulness intervention in this study is conducted by a psychological counselor who had received systematic mindfulness training. The mindfulness exercise audios are recorded by this counselor. Participants engage in mindfulness exercises through the WeChat platform and complete feedback forms there. Researchers promptly analyze mindfulness exercise feedback, address issues, and communicate with participants online, encouraging daily engagement.

### Measurement instruments

The personal information form includes two sections: demographic characteristics (age, education level, occupation, religious beliefs, income level, personality traits, marital status, living conditions, living arrangements) and obstetric characteristics (pregnancy and childbirth history, history of abnormal pregnancies, gestational age, pregnancy intentions, fertilization method, fetal abnormality diagnosis).

Mindfulness exercise feedback form created by researchers will be used to gather insights into participants’ mindfulness exercise experiences. It covers exercise duration, challenges faced, feelings during the exercise, satisfaction with the intervention (content, methodology, duration), and any suggestions for improvement.

The Generalized Anxiety Disorder Scale (GAD-7) assesses anxiety severity and functional impairment over the past two weeks with 7 items, each scored from 0 to 3. Scores range from 0 to 21, where 0–4 indicate no anxiety, 5–9 mild anxiety, 10–14 moderate anxiety, and ≥ 15 severe anxiety. The Chinese version is reliable and valid, with a Cronbach’s α of 0.92 [28].

The Patient Health Questionnaire (PHQ-9), a 9-item, 4-point scale, measures maternal depression. The PHQ-9, known for its simplicity and sensitivity, is commonly used to assess antenatal depression. Total scores, reflecting the sum of all items, indicate the severity of depressive symptoms: higher scores suggest more severe symptoms. Scoring Criteria: 0–4 points indicate no depression, 5–9 indicate mild depression, 10–14 indicate moderate depression, 15–19 indicate moderately severe depression, and above 19 indicate severe depression. The Chinese version’s Cronbach’s α coefficient, for use in pregnant is 0.89 [29].

Family Adaptation Partnership Growth Affection and Resolve index (Family APGAR), developed by Smilkstein [30] in 1978, assesses family functioning across five dimensions: adaptability, partnership, growth, affection, and resolve. It uses a 3-point rating scale: total scores of 7 to 10 signify good family functioning, 4 to 6 suggest moderate dysfunction, and 0 to 3 denote severe dysfunction. The scale has demonstrated high reliability and validity, with a Cronbach’s α coefficient of 0.85 [31]. In this study, the Family APGAR measures family support levels.

Five Facet Mindfulness Questionnaire (FFMQ) encompasses five dimensions: observation, description, conscious action, non-judgment, and non-reaction. The observation dimension aligns with mindful attention, while non-judgment and non-reaction align with acceptance. The FFMQ, consisting of 39 items rated on a five-point scale, higher total scores indicate elevated mindfulness levels. It exhibits good reliability and validity, with an internal consistency coefficient of 0.79 [32]. In this study, the FFMQ measures mindfulness levels.

### Assessments

The demographic and obstetric characteristics will be collected at baseline. Qualified couples complete the GAD-7, PHQ-9, Family APGAR, and FFMQ scales upon admission, post-intervention, and 42 days postpartum. Additionally, they are expected to complete a mindfulness exercise feedback form weekly.

Semi-structured interviews with the intervention group are conducted post-intervention and 42 days postpartum. Interviews focus on participants’ experiences, engagement and acceptance of the intervention, as well as factors facilitating their physical and mental recovery, aiming to validate and refine the intervention model.

Childbirth outcome indicators collected post-labor induction will include the duration of each labor stage, the amount of bleeding during and post-labor, and the obstetric complication rate. The study’s schedule is shown in Table 2.

**Table 2 Tab2:** Time schedule of enrollment, interventions, assessments, and follow-up for participants

	Enrolment	Allocation	Post allocation						Follow-up
Timepoint	T0	T0	T1	T2	T3	T4	T5	T6	T7
Eligibility screen	x								
Informed consent	x								
Allocation		x							
Interventions									
Intervention group			Session1	Session2	Session3	Session4	Session5	Session6	
Control group			Routine psychological care						
**Assessments**		Baseline						Post-intervention	
1.Personal information form		x							
2.Feedback form for mindfulness training				x	x	x	x	x	
3.GAD-7		x						x	x
4.PHQ-9		x						x	x
5.Family APGAR		x						x	x
6.FFMQ		x						x	x
7.Delivery outcome indicators				x					

T0: Admission day (Baseline); T1: First day post-admission; T2: Day before discharge; T3: One week post-discharge; T4: Two weeks post-discharge; T5: Three weeks post-discharge; T6: Four weeks post-discharge (Post-intervention); T7: 42 days postpartum.

### Statistical analysis

#### Sample size

To calculate the necessary sample size, the formula N1 = N2 = 2[(Zα + Zβ)S/δ]^2^ is used. Based on results from previous mindfulness intervention studies [21] on mental health symptoms, we derived values: S = 0.64, δ = 0.41, α = 0.05, and β = 0.10. Applying these values, the estimated total sample size is 104. Accounting for a 20% attrition rate and sampling error, the estimated sample size for each of the intervention and control groups is 62.

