## Setting and recruitment

Screening and enrollment of participants will occur on the admission day. This study conducted at the Women’s Hospital School of Medicine, Zhejiang University. This study aims to enroll 124 couples experiencing TOPFA, with 62 couples in both the intervention and control groups. The study’s recruitment phase was initiated on March 21, 2022, and the data collection process is projected to be finalized by October 31, 2025. The study’s flow chart is presented in Fig. 2.

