## Eligibility criteria

The inclusion criteria include: a diagnosis of fetal abnormality confirmed by Zhejiang Provincial Prenatal Diagnosis Center and a decision to terminate the pregnancy due to the fetal abnormality after > 14 gestational weeks. Couples must be over 18 years old, have no prior participation in mindfulness-related psychological interventions or other scientific research, be proficient in using WeChat, willing to accept online interventions via WeChat, and both spouses must voluntarily participate and provide signed informed consent. The exclusion criteria include: a history of psychosomatic diseases; intellectual disabilities, illiteracy, or an inability to understand the intervention and assessment content; development of severe psychosomatic issues during the study, preventing participation; voluntary withdrawal or loss of contact during the study; incomplete research questionnaires or missing items.

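### 62 couples per arm covers about 16% attrition, not the stated 20%, if the plan's own requirement of 52 per arm is to be kept; the cost is about one point of power

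*Protocol article*

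**What the plan says.** The Sample size section uses the usual formula for comparing two independent means: "To calculate the necessary sample size, the formula N1 = N2 = 2[(Zα + Zβ)S/δ", with the bracket squared. The inputs are "S = 0.64, δ = 0.41, α = 0.05, and β = 0.10". From these, "the estimated total sample size is 104", which is 52 per arm with equal groups. The section then moves to the enrolment target: "Accounting for a 20% attrition rate and sampling error, the estimated sample size for each of the intervention and control groups is 62". It shows no inflation formula and gives no size for the sampling error.

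The section on setting and recruitment repeats the target and fixes the unit as the couple: "This study aims to enroll 124 couples experiencing TOPFA, with 62 couples in both the intervention and control groups".

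The eligibility criteria bear on what attrition does to the analysed sample. Their list of exclusions includes "voluntary withdrawal or loss of contact during the study; incomplete research questionnaires or missing items".

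**The concern.** An allowance for attrition should leave the required number of couples after the stated loss. Here the required number (104), the loss (20%) and the enrolment target (62 per arm) are all printed, so the claim can be checked directly, and it fails: 80% of 62 is less than 52. The sentence also says that 62 absorbs sampling error. Any such extra allowance would push the target above what attrition alone requires, yet 62 does not reach even that.

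The attrition allowance is the yardstick for judging observed losses. As written, a reader would take losses of up to 20% to be within plan, when the requirement of 52 per arm is already missed once losses pass about 16%. Because couples who withdraw, lose contact or return incomplete questionnaires are listed as exclusions, the losses would come out of the analysed sample.

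**Working it through.** **Inputs.** From the Sample size section: S = 0.64, δ = 0.41, α = 0.05, β = 0.10, attrition 20%, 104 in total before attrition, 62 per arm after. From the section on setting and recruitment: equal allocation, the couple as unit, 124 couples. The article does not say whether α is one- or two-sided.

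**Step 1: reproduce the base figure.** With two-sided α,

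n per arm = 2 × [(1.95996 + 1.28155) × 0.64 / 0.41]² = 51.2, rounded up to 52, so 104 in total.

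This matches the article. One-sided α gives 41.7, so 42 per arm and 84 in total, which does not match. The plan is therefore two-sided, and 52 per arm is its own requirement.

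**Step 2: apply the attrition allowance.** If a proportion 0.20 is lost, enrolment must be n / (1 − 0.20).

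- From the rounded requirement: 52 / 0.8 = 65 per arm, 130 in total.
- From the unrounded requirement: 51.2 / 0.8 = 64.0 per arm, so rounding does not rescue 62.
- Stated target: 62 per arm, 124 in total, which is 3 per arm and 6 in total below 65 and 130.

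**Step 3: ask where 62 could come from.** 52 × 1.2 = 62.4, and 51.2 × 1.2 = 61.4, which rounds up to 62. Multiplying by 1.2 fits; dividing by 0.8 does not.

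**Step 4: see what 62 delivers.**

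- After 20% loss: 62 × 0.8 = 49.6 per arm; 124 × 0.8 = 99.2 in total, against 104.
- Largest loss that still leaves 52: 1 − 52/62 = 16.1%.

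**Step 5: convert to power.** By the normal approximation behind the plan's formula, power = Φ(δ / (S√(2/n)) − 1.95996).

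| Couples per arm analysed | Normal approximation | t-test (noncentral t) |
|---|---|---|
| 52 (plan's requirement) | 90.4% | 89.9% |
| 50 | 89.3% | 88.7% |
| 49.6 (62 less 20%) | 89.1% | 88.5% |
| 49 | 88.7% | 88.1% |

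With n = 49.6: 0.41 / (0.64 × √(2/49.6)) = 3.190; 3.190 − 1.960 = 1.230; Φ(1.230) = 0.891. Within one method, going from 52 to 49.6 per arm costs about 1.4 points (90.4% to 89.1%, or 89.9% to 88.5%). Against the nominal 90%, the shortfall by the plan's own method is 0.9 points.

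**The case against.** The strongest reply is that this hardly matters. The loss of about one point is smaller than the precision of the planning inputs: if S were 0.655 instead of 0.64, power at a full 52 per arm would also be 89.1%. The calculation also describes a simple comparison of two means, whereas the plan of data analysis names repeated measures ANOVA or generalized estimating equations over three time points, so neither 90% nor 89% is the power of the planned analysis. All of that stands, and it is why the point is minor. It does not make the sentence correct.

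A reader might infer three stronger things that the documents do not support.

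- *That the trial is underpowered or its 90% target defeated.* At 20% loss the plan's own formula gives about 89%, and if losses stay at or below 16.1% the requirement is fully met. Figures nearer 88% need either 49 per arm, which is 79.0% of 62 and so a 21% loss, or a change from Z values to the t-test. By the t-test even 52 per arm gives 89.9%, so part of that apparent drop comes from the change of method.
- *That the authors demonstrably multiplied by 1.2.* This is the likely explanation, but the article shows no inflation step. What can be shown is that 62 does not keep 52 after 20% loss, however 62 was reached.
- *That more couples must be enrolled.* Restating what 62 covers is enough.

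Nor can the point be put down to condensing a fuller protocol. All three numbers are printed, and no further detail makes 62 × 0.8 equal 52.

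**Conclusion.** The point holds as a minor arithmetic inconsistency. The stated 104 in total, 20% attrition and 62 per arm cannot all be true: 62 per arm leaves 49.6 at 20% loss, covers 16.1% attrition if 52 are to remain, and falls 3 per arm short of the 65 that 20% would need. Nothing is left over for sampling error. The consequence is power of about 89% at 20% attrition by the plan's formula (about 88.5% by t-test, where 52 per arm itself gives 89.9%), against the 90% implied by β = 0.10.

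This rests on taking the couple as the unit, one outcome, a simple two-mean comparison and two-sided α, as the plan's formula and its reproduced total of 104 imply, and on lost or incomplete couples leaving the analysed sample, as the eligibility criteria indicate.

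**What to change.** Replace the attrition sentence in the Sample size section with wording such as: *62 couples per arm retain 52 evaluable couples per arm with up to about 16% attrition; at 20% attrition about 49 to 50 per arm remain and power is about 89%.* Remove the claim that 62 also covers sampling error, since no number supports it. State that α is two-sided, because only that reproduces 104.

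The cost is one sentence and a slightly less favourable statement of power. Enrolment, analysis and conduct do not change. If the sponsor wishes to keep both 20% attrition and β = 0.10 as stated, the consistent target is 65 per arm, 130 couples in total, which is 6 more than planned.

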### Plan of data analysis

Statistical analyses will be performed with SPSS 19.0 software. A database will be created using a dual data entry method, with logical checks to ensure data accuracy. Categorical data will be analyzed using rates and percentages, and continuous data will be described statistically as mean ± standard deviation. Baseline characteristics of the two groups will be analyzed using non-parametric tests, chi-square tests, or independent samples t-tests. Differences in scores (GAD-7, PHQ-9, Family APGAR, FFMQ) before and after the intervention will be compared between the two groups. For normally distributed data, repeated measures ANOVA will be used; for non-normally distributed data, generalized estimating equations will be applied. The threshold for statistical significance is set at *P* < 0.05.

Interviewees will be coded sequentially according to their interview times. Audio recordings will be transcribed into text within 24 h post-interview, including documentation of non-verbal behaviors. Data will be analyzed, refined, and coded independently by at least two researchers using Colaizzi’s 7-step method. ① Reading all interview materials carefully; ② annotating important statements; ③ coding recurring viewpoints; ④ consolidating coded viewpoints into themes; ⑤ writing detailed and comprehensive descriptions; ⑥ summarizing similar viewpoints; ⑦ verifying with interviewees via phone calls, WeChat, or follow-up interviews.

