**Methods/design:**

This prospective, randomized controlled trial aims to assess the feasibility and impact of a mindfulness-based, couple-centered intervention (MBCI) on anxiety, depression, mindfulness level, and family support among bereaved parents. The study will enroll 124 couples experiencing TOPFA. Participants will be randomly assigned to either the intervention group (receiving MBCI in addition to routine psychological care) or the control group (receiving only routine psychological care). Data will be collected at three time points: baseline, post-intervention and 42 days postpartum. Additionally, participants are expected to complete a weekly mindfulness exercise feedback form. Semi-structured, in-depth interviews with the intervention group will be conducted post-intervention and 42 days postpartum.

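### A raw-score normality check picks the model for each scale, and baseline enters as an outcome level rather than a covariate; the power cost is moderate at low between-visit correlation and about nil at high

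*Protocol article*

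**What the plan says.** The Assessments section has every scale measured three times: "Qualified couples complete the GAD-7, PHQ-9, Family APGAR, and FFMQ scales upon admission, post-intervention, and 42 days postpartum". Table 2 puts these at T0 (admission day), T6 (post-intervention) and T7 (42 days postpartum). Session 1 is at T1, so T0 precedes any treatment.

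Under Plan of data analysis, the comparison is: "Differences in scores (GAD-7, PHQ-9, Family APGAR, FFMQ) before and after the intervention will be compared between the two groups". The method then depends on the data: "For normally distributed data, repeated measures ANOVA will be used; for non-normally distributed data, generalized estimating equations will be applied". Baseline otherwise appears only in the tests of group comparability: "Baseline characteristics of the two groups will be analyzed using non-parametric tests, chi-square tests, or independent samples t-tests". No baseline covariate is named for the outcome analysis. The text does not say which F-test carries the conclusion, or to which variable, visit, arm or parent the normality check applies.

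The Sample size section uses "N1 = N2 = 2[(Zα + Zβ)S/δ]^2" with "S = 0.64, δ = 0.41, α = 0.05, and β = 0.10" and concludes that "the estimated total sample size is 104".

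**The concern.** Two features of the stated method are at issue.

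**Baseline as an outcome level.** In a randomised comparison the expected group difference at T0 is zero. If T0 is a level of the time factor, the treatment effect sits in the group by time interaction. With three visits that is a 2-df omnibus test, which says that the profiles differ but gives no size of effect at T6 or T7. The T0 score would do more as a covariate, where it removes between-couple variance from the follow-up comparison.

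**Choice of model by normality.** The ANOVA assumption concerns residuals, not raw scores, and GEE is not reserved for non-normal data. With about 50 couples per arm, comparisons of means do not need normal raw scores. The rule also gives no answer when a scale looks normal at one visit and not at another. Bounded scores such as GAD-7 (0 to 21) and PHQ-9 may fail the check while the 39-item FFMQ passes, so scales within one trial could be analysed differently.

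At stake are some power, an interpretable estimate at each follow-up, and a model known before the outcomes are seen.

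**Working it through.** **1. The plan's own figure.** Inputs from Sample size: S = 0.64, δ = 0.41, α = 0.05 (two-sided assumed), β = 0.10.

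n per arm = 2 × [(1.960 + 1.282) × 0.64 / 0.41]² = 51.2, so 52 per arm and 104 in total. This reproduces the plan. A one-sided α gives 42 per arm (84 in total) and does not. The formula is a two-mean comparison at one time, with no term for baseline or for correlation between visits.

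**2. Assumptions for the power comparison.** 52 per arm with one score per couple; standardised effect d = 0.41/0.64 = 0.6406; compound symmetry with correlation rho. The article gives no rho, so I show 0.3, 0.5 and 0.7.

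**3. Formulas** (noncentral F, α = 0.05):
- Group by time, 2 and 204 df: λ = (n/2) × Σ(eₜ − ē)² / (1 − rho). For the sustained effect (0, d, d), Σ(eₜ − ē)² = (2/3)d² = 0.2736, so λ = 26 × 0.2736 / (1 − rho) = 10.2, 14.2, 23.7.
- Baseline-adjusted at T6: λ = (n/2) × d² / (1 − rho²) = 11.7, 14.2, 20.9, with 1 df.
- Group main effect over three visits: the effect shrinks to (2/3)d = 0.427, with variance (1 + 2rho)/3, so λ = 8.9, 7.1, 5.9, with 1 df.

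**4. Results.**

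| Test | rho 0.3 | rho 0.5 | rho 0.7 |
|---|---|---|---|
| Group by time, sustained effect | 82% | 93% | 99% |
| Baseline-adjusted at T6 | 92% | 96% | 99% |
| Group main effect, sustained effect | 84% | 75% | 67% |
| Group by time, effect halved by T7 | 69% | 84% | 97% |
| Baseline-adjusted at T7, effect halved by T7 | 40% | 46% | 62% |

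The gap between the first two rows is 10 points at rho 0.3, about 3 at 0.5, and nil at 0.7.

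**5. Sample size with baseline adjustment at one visit.** 51.2 × (1 − rho²) gives 47, 39 and 27 per arm at rho 0.3, 0.5 and 0.7, against 52 in the plan.

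**6. The switch.** Simulation with 4,000 runs per scenario, 52 per arm and rho 0.6: Shapiro-Wilk at each visit, then repeated measures ANOVA if none rejects, otherwise a robust Wald GEE test.

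| Data | Type I error, two-stage rule | ANOVA alone | GEE alone | Normality rejected |
|---|---|---|---|---|
| Normal | 0.052 | 0.051 | 0.058 | 14% |
| Moderate skew | 0.061 | 0.050 | 0.061 | about 100% |
| Floor-type counts | 0.056 | 0.047 | 0.056 | about 100% |

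The small excess comes from the robust GEE test at this sample size rather than from the act of choosing. With truly normal data, chance alone changes the model in about one trial in seven.

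**The case against.** The strongest reply is that the power loss is conditional. Comparing before/after differences between groups points to group by time, not to the group main effect. On group by time the planned test exceeds the stated 90% from rho 0.5 upward and matches baseline adjustment at 0.7. That stands. A reader might take the 84%, 75% and 67% for the main effect as the plan's power. The article does not say the main effect carries the conclusion, so these figures show only what would follow if it were read that way.

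A reader might also infer that the switch seriously inflates false positives. It does not: the simulated error is about 0.05 to 0.06.

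Nor should the repeated measures ANOVA be blamed for losing couples with a missed visit. Eligibility criteria already lists loss of contact, withdrawal and incomplete questionnaires as exclusions, so the analysis set is close to completers under either model.

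The two-mean sample size formula is a common simplification and is conservative for a baseline-adjusted analysis (52 against 47, 39 or 27 per arm). The mismatch means that the 90% describes neither planned test; it does not mean the trial is too small.

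Baseline adjustment also needs a stated target. If the effect halves by T7, a T7 contrast has only 40% to 62% power. It would therefore be unfair to set an omnibus test over both visits against whichever single contrast happens to look best.

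Finally, details such as covariates and the form of the normality check may sit in an analysis plan not shown here. That excuses missing detail, but not the switch itself, which the article states as the rule.

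**Conclusion.** The point holds in a limited form. The article makes the model depend on a raw-score normality check that is not needed at this size, and it leaves the baseline score out as a covariate. Baseline as a level of the time factor is the plain reading of a before/after comparison over three visits, but it is not stated in words.

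On group by time the power loss against a baseline-adjusted T6 comparison is moderate at low correlation (82% against 92% at rho 0.3), small at 0.5 (93% against 96%) and about nil at 0.7. These figures rest on 52 per arm, a sustained 0.64 SD effect, compound symmetry, an assumed rho and one score per couple. Correlation between partners is not addressed by them.

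The more lasting costs do not depend on rho: the model is not fixed before the data are seen, it can differ between scales, and the omnibus test gives no effect estimate at either follow-up. The change should be made, but the documents do not support a claim of general power failure or of material type I error inflation.

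**What to change.** Prespecify one model for GAD-7, PHQ-9, Family APGAR and FFMQ, to be used whatever a normality check shows:

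- **Outcomes:** scores at T6 and T7.
- **Terms:** baseline score, arm, time, arm by time and baseline by time, with the couple structure represented.
- **Deciding contrast:** one named time point, for example T6 (post-intervention), chosen before outcome data are examined. An unweighted average of T6 and T7 is not a safe default: if the effect is present only at T6, its baseline-adjusted power is about 59%, 64% and 78% at rho 0.3, 0.5 and 0.7 (normal approximation).
- **Reporting:** adjusted mean difference with 95% CI at T6 and at T7.
- **Check for skewed scores:** robust or bootstrap standard errors on the same model, in place of a change of method.

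The cost is analysis wording plus an ethics resubmission, because Protocol amendments requires one for any modification. All the scores needed are already scheduled, so no new data are required.

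### No primary outcome is named among four scales each compared at P < 0.05, and the S and δ behind the 90% power are assigned to no scale, parent or visit

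*Protocol article*

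**What the plan says.** - **Aim.** The Abstract (Methods/design) sets out to assess feasibility and the effect of the intervention "on anxiety, depression, mindfulness level, and family support among bereaved parents". The Introduction repeats the aim. The four domains stand side by side, and no outcome is called primary anywhere in the article.
- **Analysis.** Plan of data analysis compares scores on GAD-7, PHQ-9, Family APGAR and FFMQ between the groups, by repeated measures ANOVA if the data are normal and by generalized estimating equations if not. One rule covers everything: "The threshold for statistical significance is set at" P < 0.05. The section does not say which scale, parent, visit or model effect decides the trial.
- **Measurement.** Under Assessments and in Table 2, both parents complete all four scales at baseline, post-intervention (T6) and 42 days postpartum (T7).
- **Sample size.** "Based on results from previous mindfulness intervention studies [21] on mental health symptoms, we derived values", namely "S = 0.64, δ = 0.41, α = 0.05, and β = 0.10". Then "the formula N1 = N2 = 2[(Zα + Zβ)S/δ]^2^ is used", and "the estimated total sample size is 104". No scale, parent or visit is attached to S or δ.
- **Scoring.** Measurement instruments describes each scale by a total: GAD-7 from 0 to 21, PHQ-9 as the sum of nine items, Family APGAR in bands from 0 to 10, and FFMQ as a total over 39 five-point items.

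**The concern.** An error rate and a power belong to a stated decision. Here the article gives α, β, S, δ and N but not the comparison they serve. Two things follow.

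First, the article says the intervention could enter clinical care if it proves effective (Abstract, Discussion) without saying what result on the four scales would show that. One reading inflates the false-positive rate above 5%. The other lowers the power below 90%.

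Second, a reader cannot tell what difference, on which questionnaire, the trial is sized to detect.

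Timing makes this more than a matter of wording. Recruitment began in March 2022, data collection is projected to end in October 2025, and the Discussion acknowledges that the study is not blinded. A primary chosen after the group results have been seen would not restore the 5% rate.

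**Working it through.** **Inputs** (Sample size): α = 0.05, β = 0.10, S = 0.64, δ = 0.41, 1:1 allocation, 20% attrition, 62 per group. From Plan of data analysis: four scales, each compared at 0.05. Assumed, because the article gives no values: pairwise correlations of 0.3 to 0.7 between the test statistics, PHQ-9 items scored 0–3 (total 0–27), and FFMQ items scored 1–5 (total 39–195).

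**1. The plan's own figure.** 2 × [(1.960 + 1.282) × 0.64 / 0.41]² = 51.2, rounded up to 52 per group, or 104 in total. This matches the stated figure with a two-sided α. A one-sided α gives 42 per group (84 in total) and does not match. The formula uses only the ratio δ/S = 0.41/0.64 = 0.64, so 104 is right for any single outcome with that standardised effect.

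**2. If any one of the four scales suffices.** With independent tests the chance of at least one false positive is 1 − 0.95⁴ = 18.5%. A simulation of equally correlated normal test statistics (400,000 draws) gives:

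| Correlation | Chance of at least one false positive, 4 tests |
|---|---|
| 0.3 | 17.4% |
| 0.5 | 15.7% |
| 0.7 | 12.9% |

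**3. If all four must succeed.** With 90% power on each, joint power is 0.9⁴ = 66% if independent. Positive correlation raises it, but it reaches 90% only if the four tests are fully dependent.

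**4. What the text leaves open.** It does not say whether mothers and fathers, or T6 and T7, are tested separately. If they were, the independent figures would be:
- 4 scales × 2 parents: 1 − 0.95⁸ = 34%
- 4 scales × 2 parents × 2 visits: 1 − 0.95¹⁶ = 56%

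At correlations of 0.7–0.3 these become 19–30% and 26–48%.

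**5. S and δ against the scales.**

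| Scale | S, δ as % of total range | S, δ on the total if 0.64 and 0.41 are item means |
|---|---|---|
| GAD-7 (0–21) | 3.0, 2.0 | ×7: 4.5, 2.9 |
| PHQ-9 (0–27) | 2.4, 1.5 | ×9: 5.8, 3.7 |
| Family APGAR (0–10) | 6.4, 4.1 | ×5: 3.2, 2.05 |
| FFMQ (39–195) | 0.4, 0.3 | ×39: 25, 16 |

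Read as total-score units, δ is under half a point on scales scored in whole points. If scores were roughly normal, about 95% of participants would lie within ±1.96 × 0.64 = ±1.25 points. That span of 2.5 points is half of one five-point GAD-7 severity band. The Introduction's prevalence figures for mothers (24.3% anxiety, 50.3% depression) suggest a much wider spread. Read as item means, the values are possible.

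**6. Price of keeping all four confirmatory.** With Bonferroni at 0.05/4 = 0.0125 and δ/S = 0.64, power is Φ(0.6406 × √(52/2) − 2.498) = Φ(0.769) = 78% with 52 evaluable per group. With 62 × 0.8 = 49.6 per group it is 76%. Keeping 90% needs 70 evaluable per group, or 88 enrolled at 20% loss (70/0.8 = 87.5).

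**The case against.** - **Number of tests.** A reader might infer that every scale is tested in each parent at each later visit, giving 16 tests and a 56% risk. The text does not support this. The visits enter one repeated measures ANOVA or GEE, and no separate test by parent or visit is stated. The plan fixes four scale-level comparisons, so 34% and 56% are what-ifs.
- **Independence.** The Introduction reports correlated anxiety, depression and PTSD levels in both parents, so 18.5% is an upper bound and 13–17% is the better guide.
- **S and δ.** A reader might infer that they fit none of the scales. The article gives no standard deviation for any scale, and item means would give possible values. What can be said is that they are assigned to no scale and are implausible as total-score units.
- **Power.** A reader might infer that the 90% applies to nothing. That goes too far, because it holds for any single outcome with δ/S = 0.64. What is missing is the outcome for which that effect is expected.
- **Success rule.** The article does not state that one significant scale is enough. The Discussion lists several improvements together, which could mean that all are required. That reading avoids the inflation but lowers the power.
- **What belongs elsewhere.** A multiplicity procedure can be left to an SAP, and the registration, which is not at hand, may name a primary. The lack of an adjustment is therefore not the finding. The outcome on which N rests is a design choice, and an article that prints the whole power calculation should say what it is for. This part of the concern stands.

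**Conclusion.** The point holds in this form: no primary outcome is named among four scales each compared at P < 0.05, and S = 0.64 and δ = 0.41 are assigned to no scale, parent or visit.

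The size depends on a success rule that the article does not give. If any one scale suffices, the false-positive chance is about 13–17% at assumed correlations of 0.7–0.3, and at most 18.5% for the four stated comparisons if they are independent or positively correlated. If all four must succeed, joint power is below 90%, and 66% under independence with 90% on each scale.

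The arithmetic of the 104 is correct. The defect is that it cannot be linked to a named outcome or to a difference in that outcome's units.

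**What to change.** Before any comparative look at the data:

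1. Name one primary: one scale, one population (for example mothers, or a couple-level effect), and one visit or the group-by-time effect, tested at two-sided 0.05. If the registration names a primary, carry it over.
2. State S and δ in that scale's units, with the source, and say whether the present values are item means or totals.
3. Label the other comparisons secondary, either Holm-adjusted as one family or reported as estimates with confidence intervals and no claim.
4. Let the word 'effective' in the Abstract and Discussion depend on the primary alone.

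The cost is a protocol amendment, which under Protocol amendments must go back to the ethics committee, and some work to recover the source values for S and δ. A couple-level primary would also need a model for the two partners that Plan of data analysis does not now specify. A significant secondary scale alone could no longer support a claim of effectiveness. No extra couples are needed if δ/S = 0.64 holds for the chosen primary.
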